#### Data collection

Data on *impact outcomes* will be obtained through a clinical examination of children and a telephone survey of parents/caregivers and children at baseline and after 24 months. A random sample of Medicaid-enrolled ADS-assigned children will be obtained and stratified by county, at baseline and 24 months post-implementation. The sample will include children whose caregivers either consented or did not consent for care. It will also include children who sought care directly from a dental office. For the survey, staff members will be given a list of enrollees to telephone and move down the list in order until the required sample size is reached. Each individual will be called a minimum of five times. For the clinical examination, staff members will be given a list of enrollees, and they will exam the children in the community settings.

Data on *process and cost outcomes* will be obtained through ADS’s health information systems: Medicaid enrollment database, ADS database (ADIN), electronic dental records and payroll ledger. All Medicaid-enrolled ADS-assigned children population will be included in the process and cost evaluation. Enrollment information including patient identifiers, birth date, gender, race/ ethnicity, coverage dates and assigned primary care provider will be obtained from ADS’s enrollment database and linked to State Medicaid claims. Medicaid claims will be accessed to collect emergency department, medical care and prescription services and costs. Data on *structure outcomes* will be obtained through staff online surveys at baseline and after 24 months and continuously through ADS’s health information systems and internal records. Fidelity information will be obtained through staff surveys and internal records.

### Statistical analysis

#### Sample size

Based on seven test counties and seven control counties, the power is at least 80 % to detect an increase in dental care utilization from pre- to post-implementation within the test counties or an increase in utilization between test and control counties post-implementation of approximately 10 percentage points for utilization rates of 5 % to 10 %, 15 percentage points for utilization rates of 20 % to 30 %, and 20 percentage points for utilization rates of 40 % to 50 %. Estimates are conservative, based on an intracounty correlation (ICC) of 0.05. Pilot data on dental care utilization indicated ICCs were less than 0.05 for cluster sizes of 200 or more children, and ICCs were less than 0.02 for cluster sizes greater than 500 children. Using a sample size of 80 children per county pre- and post-implementation and an ICC of 0.05, we estimate power is 80 % to demonstrate a 15 percentage point or larger decrease in prevalence of untreated dental caries, assuming a prevalence of untreated caries of 25 % in the control counties. In 2012, 25 % of 6 to 10 years old from low-income families in Oregon had untreated dental decay [28]. Using a sample size of 20 parents per county pre- and post-implementation we estimate power is 84 %, based on a two-sided 0.05 significance level, to detect a medium effect of the intervention on dental care ratings (for example, an average increase of 0.75 points) (CAHPS; range 1 to 10), assuming SD = 1.5 in patient satisfaction scores [29].

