#### Randomization and blinding

Each County is considered a single cluster. Clusters are randomized with equal probability to the test or control interventions, using computer-generated random numbers. The allocation schedule for random assignment is generated at the University of Washington by the project biostatistician. The treatment allocation for each cluster is kept in Seattle, and the biostatistician informs local investigators about the treatment allocation, when they are ready to conduct the environmental scan of the test sites. Interviewers are blinded to group allocation. Because of the type of the intervention, personnel involved in the delivery of the intervention and participants are not blinded to group allocation.

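### At the stated ICC of 0.05, 14 counties do not give 80% power for the listed test-versus-control utilization differences at rates of 10% and 30%

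*Protocol article*

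**What the plan says.** Under Randomization and blinding, the protocol article makes the county the unit of allocation: "Each County is considered a single cluster". On utilization, the Sample size section says: "Based on seven test counties and seven control counties, the power is at least 80"%. The claim covers a pre-to-post change within test counties, "or an increase in utilization between test and control counties post-implementation". The effects are "approximately 10 percentage points for utilization rates of 5"% to 10%, then 15 points for 20% to 30% and 20 points for 40% to 50%. The basis is given as "Estimates are conservative, based on an intracounty correlation (ICC) of 0.05", with pilot support: "ICCs were less than 0.02 for cluster sizes greater than 500 children".

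The same section gives 80% power for untreated caries (80 children per county, ICC 0.05, 25% in control counties, a 15-point decrease). For the survey it says "Using a sample size of 20 parents per county pre- and post-implementation we estimate power is 84"%, for a 0.75-point effect with SD 1.5 at a two-sided 0.05 level. No ICC accompanies the survey figure.

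**The concern.** With seven counties per arm and an ICC of 0.05, variation between counties sets a floor on the standard error that more children cannot lower. The utilization claim is made for ranges of rates, and a binomial variance rises across the first two ranges while the effect is held fixed. Power must therefore fall towards 10% and 30%. If it falls well below 80% there, the stated power does not follow from the stated inputs.

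Utilization is a primary process outcome in Table 1. A reader told that power is at least 80% on conservative assumptions would read a null result as good evidence against an effect of that size. The survey figure raises a related question: whether 84% allows for the comparison resting on only 14 counties.

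**Working it through.** **Inputs.** Seven counties per arm, ICC 0.05, and the listed rates and effects (Sample size). Process outcomes use the whole assigned population (Data collection), so average county size is m = 82,000/14 ≈ 5,857; this assumes equal counties and includes pregnant women. Two-sided 0.05 is stated for the survey only and is assumed elsewhere.

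**Method.** Effective n per arm = 7m / [1 + (m − 1) × ICC]. SE = √{[p₁(1 − p₁) + p₂(1 − p₂)] / effective n}. Noncentrality = (p₂ − p₁)/SE. Power is taken from a normal reference and from a noncentral t on 14 − 2 = 12 df.

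**The protocol's caries figure first.** Effective n = 560/(1 + 79 × 0.05) = 560/4.95 = 113.1. For 25% versus 10%, SE = √(0.2775/113.1) = 0.0495 and noncentrality = 0.15/0.0495 = 3.03. Power is 79.4% on 12 df, matching the stated 80%. The normal reference gives about 85 to 86%, which does not match.

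**Utilization, test versus control, post-implementation.** Effective n = 7 × 5,857/(1 + 5,856 × 0.05) = 139.5. Its limit is 7/0.05 = 140.

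| Rates | SE | Noncentrality | Normal | 12 df |
|---|---|---|---|---|
| 5 to 15% | 0.0354 | 2.82 | 81% | 74% |
| 10 to 20% | 0.0423 | 2.36 | 66% | 58% |
| 20 to 35% | 0.0527 | 2.85 | 81% | 74% |
| 30 to 45% | 0.0573 | 2.62 | 75% | 67% |
| 40 to 60% | 0.0586 | 3.41 | 93% | 88% |
| 50 to 70% | 0.0574 | 3.48 | 94% | 89% |

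Taking every whole-percent rate in the three bands (28 rates), 17 fall below 80% on 12 df, namely all of the first two bands. With a normal reference the count is 14 (unpooled variance) or 16 (pooled).

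**Increase needed for 80% power** (effective n 140), in points:

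| Starting rate | Normal | 12 df |
|---|---|---|
| 5% | 9.9 | 11.0 |
| 10% | 12.1 | 13.4 |
| 20% | 14.7 | 16.1 |
| 30% | 16.0 | 17.5 |
| 40% | 16.5 | 17.9 |
| 50% | 16.3 | 17.7 |

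**At the pilot ICC of 0.02.** With m = 500, effective n = 3,500/(1 + 499 × 0.02) = 318.8, and power on 12 df runs from 90.5% (10 to 20%) to 99.8% (50 to 70%). With m = 5,857 the lowest value is 92.7%.

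**Parent survey.** There are 7 × 20 = 140 parents per arm per time point. Two routes come close to 84%:

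- Difference in differences with independent parents: SE = 1.5 × √(4/140) = 0.2535; noncentrality = 0.75/0.2535 = 2.96; power 84.1% with a normal reference and 77.5% on 12 df.
- Post-implementation only with ICC 0.05: effective n = 140/(1 + 19 × 0.05) = 71.8; SE = 1.5 × √(2/71.8) = 0.2504; noncentrality = 3.00; power 84.5 to 85.0% with individual-level df or a normal reference, and 78.5% on 12 df.

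On 12 df, 80% power needs a noncentrality of 3.05. That is 3.05 × 0.2535 = 0.77 points by the first route and 3.05 × 0.2504 = 0.76 by the second.

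**The case against.** Several points can be made for the protocol.

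- **Reference distribution.** None is stated for utilization. With a normal reference, four of the six band endpoints reach 80%. This stands against any claim that most of the listed rates fail whatever the method; that is clear only on 12 df. It does not help 10% or 30%.
- **Approximate effects.** The effect sizes are described as approximate. That covers 5% and 20% with a normal reference and arguably 30%, which is 1 point short. It does not cover 10%, which needs 12 to 13 points.
- **Other variants.** Using the control-rate variance in both arms with a normal reference gives about 79.5% at 10% and 78% at 30%, but this understates the variance at the higher rate. A one-sided 0.05 normal test lifts every endpoint above 80% except 10%, which stays at 76%.
- **Baseline data.** The planned multilevel model uses pre and post data. If the county-level correlation over time were 0.7 (an assumption), baseline adjustment would give about 85% at 10% and 92% at 30%. No correlation is stated, and the power claim is worded for the post-implementation comparison.
- **The within-test limb.** The pre-to-post claim cannot be called wrong. On 6 df it gives 51 to 83% at a county correlation of 0 and 79 to 98% at 0.5.
- **The ICC itself.** A reader might infer that 0.05 is not conservative, or that the trial is truly underpowered for utilization. The documents support neither, given pilot ICCs below 0.02 for large clusters.
- **The survey.** A reader might conclude that clustering was certainly ignored. That is only an inference from the reproduction: a post-only calculation on 12 df with an unstated ICC of about 0.036 would also give 84%.

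**Conclusion.** The claim of at least 80% power does not follow from the protocol's own inputs for the post-implementation test-versus-control comparison. At ICC 0.05 it fails at 10% (58 to 66%) and at 30% (67 to 75%) under standard two-sided calculations that use both rates. It fails throughout the 5-10% and 20-30% bands under the 12-df calculation that reproduces the caries figure. The 40-50% band holds either way.

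The survey's 84% matches calculations that lack county-level degrees of freedom; on 12 df they give 77.5 to 78.5%.

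This rests on a two-sided 0.05 level for utilization, equal county sizes and no credit for baseline data. The fault lies in the published calculation more than in likely power: at the pilot ICC of 0.02 the listed effects have about 90% power or more.

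**What to change.** In the Sample size section, do one of the following for the test-versus-control comparison:

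- Restate the increases detectable with 80% power at ICC 0.05 and 12 df as about 11 to 13 points for rates of 5-10%, 16 to 18 points for 20-30%, and 18 points for 40-50%.
- Keep the listed effects, but say that they carry at least about 90% power at the pilot ICC of 0.02, and do not claim at least 80% at 0.05.

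State sidedness and the reference distribution. For the within-test limb, give the county-level correlation assumed. Restate the survey power as about 78% on 12 df for 0.75 points (80% at about 0.77), with the assumed ICC. The ICC of 0.05 may still be called a conservative input.

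The cost is revised text only. The sample, design and analysis do not change.

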#### Statistical analysis plan

Descriptive statistics (means, standard deviations, counts, and percentages) are calculated for all variables of interest overall and stratified by age group. The primary hypothesis is that the test intervention participants will have lower number of untreated dental caries than the control participants and the absolute changes indicate a reduction in disparities. Multilevel regression are used to assess for changes in the impact and process outcomes between pre- and post-implementation in the test and control counties, weighted by the number of eligible children/pregnant women in the county at each time point and adjusting for within-county correlation between pre- and post-implementation outcomes [30]. We use multilevel linear regression for mean scores and multilevel binomial regression for binary measures. Additional multilevel regression modeling are used to compare changes in the impact and process outcomes by child age category (for example, 0 to 5, 6 to 15 and 16 to 20 years old) or race/ethnicity, adjusting for clustering within county and weighting by number of eligible children in each age or race/ethnicity category.

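### The 80% power for the primary caries outcome was worked out for an unweighted post-only comparison, not for the population-weighted pre-to-post analysis that the plan describes

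*Protocol article*

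**What the plan says.** The article's Data collection section separates two kinds of outcome. Impact outcomes, which include the primary outcome of untreated caries, come from a random sample drawn within each county at baseline and at 24 months. Process and cost outcomes use everyone enrolled.

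The Sample size section plans the caries comparison for seven counties per arm and gives these inputs: "Using a sample size of 80 children per county pre- and post-implementation and an ICC of 0.05". On that basis the section concludes: "we estimate power is 80 % to demonstrate a 15 percentage point or larger decrease in prevalence of untreated dental caries". It takes control prevalence to be 25%.

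The Statistical analysis plan section then gives one model for both kinds of outcome. It is a multilevel regression (binomial for binary measures) of changes from before to after implementation, compared across the two arms. The fit is "weighted by the number of eligible children/pregnant women in the county at each time point". The allowance it names for clustering reads: "adjusting for within-county correlation between pre- and post-implementation outcomes". The section does not say what the weights do for a sampled outcome. The Sample size section gives no pre-post correlation and no variation in county size.

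**The concern.** Two things do not fit together.

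- **Weights.** For process outcomes the eligible population is the true denominator. For caries, a county's information lies in its roughly 80 examined children, about one seventy-third of its mean eligible population. The same sentence covers both. If the weight acts as a sampling weight, it costs some precision. If it acts as a count, the model sees far more children than were examined.
- **Power.** A comparison of change between independent samples carries the sampling and county noise of two time points. It gains only as far as true county prevalence is stable over time. A power figure computed without that correlation, and without unequal weights, does not describe the planned test.

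With only 14 clusters, the trial's ability to answer its primary question depends on both.

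**Working it through.** **Inputs from the article.** k = 7 counties per arm; m = 80 children per county at each time point; ICC = 0.05; prevalence 25% against 10%; eligible population 82,000 in 14 counties. **Assumed.** Two-sided 0.05 (stated only for the satisfaction outcome); 25% at baseline in both arms; independent samples at the two time points; ρ, the pre-post correlation of true county prevalence; CV, the coefficient of variation of county size.

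**1. Reproducing the 80%.** Write v(p) = p(1−p), so v(0.25) = 0.1875 and v(0.10) = 0.09.
- Design effect: 1 + 79 × 0.05 = 4.95.
- Two proportions with continuity correction need 113 children per arm: 113 × 4.95 / 7 = 79.9 per county, against the stated 80.
- Variance factor per county: c = 0.05 + 0.95/80 = 0.061875. SE = √[(0.1875 + 0.09) × 0.061875 / 7] = 0.0495. With 0.15/0.0495 = 3.03, the noncentral t on 12 df gives 79.4%.

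Both routes match. Both are unweighted, use one time point and contain no pre-post term.

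**2. Change analysis, unweighted.** Per-arm variance is [(v₀ + v₁)c − 2ρ × 0.05 × √(v₀v₁)] / 7, with v₀ and v₁ the values of v(p) before and after implementation. At ρ = 0.5 the brackets are 0.01383 (control) and 0.01068 (test), so SE = √(0.02450/7) = 0.0592.

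| ρ | SE | Power (t, 12 df) |
|---|---|---|
| 0 | 0.0759 | 44% |
| 0.5 | 0.0592 | 64% |
| 0.74 | 0.0491 | 80% |
| 0.8 | 0.0463 | 84% |
| 0.9 | 0.0411 | 92% |

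**3. Adding population weights.** The between-county share of a county's variance is 0.05/0.061875 = 81%, so near-equal weights are the efficient ones. Weighting by size leaves about k/(1 + CV²) effective counties per arm. At CV 0.6 that is 7/1.36 = 5.15. At ρ = 0.5 the SE becomes 0.0592 × √(7/5.15) = 0.0690 and power 52%. At CV 0.5, power is 55% at ρ = 0.5 and 76% at ρ = 0.8.

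**4. If the weights were binomial counts with only a county intercept.** Mean eligible population is 82,000/14 = 5,857, and 5,857/80 = 73. With no effect, the model SE would be √[4 × 0.1875 / (7 × 5,857)] = 0.0043. The true SE is √[2(2 × 0.1875c − 2ρ × 0.05 × 0.1875)/7], which is 0.0425 at ρ = 0.9 and 0.0629 at ρ = 0.5. The ratio is about 10 to 15, which corresponds to a false-positive rate of 84% to 89%. In simulation, unweighted county-level change scores with t on 12 df hold about 5%.

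**5. Baseline-adjusted comparison, unweighted.** The county-level correlation is r = ρ × 0.81. The post-only variance is multiplied by (1 − r²) and by 1 + 1/(14 − 4) = 1.1 for estimating the baseline slope, with t on 11 df.

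| ρ | SE | Power |
|---|---|---|
| 0 | 0.0519 | 75% |
| 0.5 | 0.0475 | 82% |
| 0.8 | 0.0396 | 93% |
| 0.9 | 0.0357 | 97% |

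**The case against.** A reader might infer from step 4 that the trial will produce false positives at an extreme rate. The article does not support that. It needs population counts used as denominators for 80 children and a county intercept as the only random effect, and the section states neither. The model is multilevel and allows for pre-post correlation within county. With proper sampling weights and county-by-period variation, the problem disappears. The article leaves this reading open but does not adopt it.

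A reader might also infer that population weighting is a mistake. It is not. With the same sample size in every county whatever its population, weighting by eligible children is ordinary design weighting, and Table 1 defines the outcome as a proportion of all assigned children. Equal county weights are more efficient but target the average county, so the choice is a trade-off.

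Third, a reader might infer that power falls short of 80%. That is not shown. Unweighted, change has more than 80% power once ρ exceeds about 0.74. The section does not say whether baseline enters as a change score or a covariate. The primary hypothesis is worded as test against control, which is the contrast whose power does reproduce.

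Random-effect structure and degrees of freedom are matters that a full analysis plan may settle. What stands is what the article itself fixes: one weight and one change model for an outcome from a small fixed sample, beside a power figure for a different, unweighted analysis.

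**Conclusion.** The concern holds as a mismatch between the power statement and the analysis. The 80% belongs to an unweighted post-only comparison. For change as worded, unweighted power ranges from 44% to 92% as ρ goes from 0 to 0.9, and weighting takes it lower to an extent set by county sizes that the article does not list. Power for the stated analysis is therefore undetermined.

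The role of the weights for caries needs stating, because the readings left open run from a modest loss of precision to standard errors too small by an order of magnitude. These sizes rest on the assumed values of ρ and CV, on 25% baseline prevalence in both arms, on independent samples at the two time points, and on a two-sided 0.05 test.

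**What to change.** - For caries, take the number of children examined as the binomial denominator. Use eligible population only as a rescaled sampling weight, and report the equal-weight estimate as a sensitivity analysis.
- Allow county-by-period variation and refer tests to county-level degrees of freedom.
- Name the primary contrast as 24-month prevalence between arms, adjusted for the county's baseline prevalence. At every ρ in the tables above, this has more power than change.
- Restate power for that weighted analysis, with a stated pre-post correlation and the actual county sizes.

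This changes wording and calculation only; the baseline is already collected. It costs one degree of freedom for the baseline term, a small loss if ρ is near 0 (75% against 79% for post-only). The restated power may also be less favourable than 80% once the weights are included.

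### The binary-outcome model names only a pre-post county correlation; if that is fitted as a single county random intercept, county-by-period variation drops out of the error term and the 5% test is too liberal

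*Protocol article*

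**What the plan says.** The county is the unit of randomisation: "Each County is considered a single cluster" (Randomization and blinding). The sample size section works from seven counties per arm and, for the primary outcome, states: "Using a sample size of 80 children per county pre- and post-implementation and an ICC of 0.05". It calls the ICC of 0.05 conservative and reports from pilot utilisation data that "ICCs were less than 0.02 for cluster sizes greater than 500 children".

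The Statistical analysis plan section compares pre-to-post changes in test and control counties by multilevel regression, with "multilevel binomial regression for binary measures". The models are weighted by the number of eligible people in each county at each time point. The county-level adjustment named for the main models is "adjusting for within-county correlation between pre- and post-implementation outcomes". The section lists no random effects and neither names nor rules out a county-by-period term.

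The caries outcome is measured on samples. For the other main set of outcomes, Data collection says: "All Medicaid-enrolled ADS-assigned children population will be included in the process and cost evaluation". The primary impact outcome and all five primary process outcomes in Table 1 are proportions, so the binomial model applies to each of them.

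**The concern.** In a comparison of change, a county's stable level cancels. What remains at cluster level is how far each county's true rate moves between the two periods for reasons unrelated to the intervention. With 14 randomised counties, that movement belongs in the error term.

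A single county random intercept does not represent it. A linear model on county-period means would have a residual to absorb it. A binomial model does not, because its variance is fixed by the mean. The arm-by-period term would then carry the standard error of independent children. The consequence grows with the number of people per county, so it is worst for outcomes measured on the whole enrolled population. There, ordinary county drift could be declared a benefit or a harm of the intervention.

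**Working it through.** **Inputs.** Seven counties per arm, 80 children per county-period, ICC 0.05, pilot ICC below 0.02 for clusters over 500, and control caries prevalence 25% with a 15-point decrease (all from Sample size). The population is about 82,000 in 14 counties, so the mean is 82,000/14 = 5,857 per county. Two-sided alpha of 0.05 is stated for the satisfaction outcome and assumed here for the others. CAC, the correlation of a county's true level between pre and post, is not in the article and is varied.

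**The plan's own figure.** Design effect = 1 + 79 × 0.05 = 4.95. Effective size per arm = 560/4.95 = 113.1. For 25% against 10%, the standard error is √[(0.1875 + 0.09)/113.1] = 0.0495, and 0.15/0.0495 = 3.03. With t on 12 df the power is 79.4%, which matches the stated 80%. This is a post-only comparison of arms that keeps the full within-period county variance in the error term.

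**Variance of the change contrast.** With m people per county-period, prevalence p and no effect:

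- True: (4/7) × p(1−p) × [ICC(1−CAC) + (1−ICC)/m]
- County intercept only: (4/7) × p(1−p) × (1−ICC)/m
- Ratio: R = 1 + m × ICC × (1−CAC)/(1−ICC)
- False-positive rate = 2 × [1 − Φ(1.96/√R)]

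Caries at CAC 0.8: R = 1 + 80 × 0.05 × 0.2/0.95 = 1.84, and 1.96/√1.84 = 1.44, which gives 15%. Process outcomes at ICC 0.02 and CAC 0.95: R = 1 + 5,857 × 0.02 × 0.05/0.98 = 6.98, and 1.96/√6.98 = 0.74, which gives 46%.

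| CAC | Caries (m = 80, ICC 0.05): R | Rate | Process (m = 5,857, ICC 0.02): R | Rate |
|---|---|---|---|---|
| 1.0 | 1.00 | 5% | 1.00 | 5% |
| 0.99 | 1.04 | 5.5% | 2.20 | 19% |
| 0.95 | 1.21 | 7.5% | 6.98 | 46% |
| 0.9 | 1.42 | 10% | 12.95 | 59% |
| 0.8 | 1.84 | 15% | 24.91 | 69% |
| 0.5 | 3.11 | 27% | 60.77 | 80% |

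**Sensitivity for process outcomes.** The value 0.02 is an upper bound from the pilot. At an assumed ICC of 0.005 the rate is 8.5% at CAC 0.99, 21% at 0.95 and 45.5% at 0.8. A county of 1,000 at ICC 0.02 and CAC 0.95 gives R = 2.02 and 17%. Outcomes with restricted denominators (referred children, pregnant women) have smaller clusters and less inflation.

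**Simulation** (1,000 trials per setting, equal county sizes, no weights). A random-intercept logistic model for caries rejected in 4.6%, 9.2%, 15.0% and 24.1% of null trials at CAC 1.0, 0.9, 0.8 and 0.5. For process outcomes at ICC 0.02 and CAC 0.8 it rejected in 68.9%. A t test on the 14 county changes rejected in 4–6% in every setting.

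**The case against.** The strongest reply is that the article does not specify an intercept-only model. A correlation between a county's pre and post outcomes could equally describe two correlated county-period effects, which would carry the missing variance. A lone intercept forces the county-level correlation to be 1, so speaking of adjustment for a correlation need not imply it. Weights per county and time point suggest 28 county-period records. The subgroup and cost analyses also mention clustering within county. The cited method source and any separate analysis plan are not shown, and random-effects detail is often left to them.

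Part of this stands. A reader might infer that the plan has fixed an invalid test; the wording does not support that, because it leaves the correlated-effects model open. A reader might also infer that process outcomes face rates near 80%. That needs either the planning ICC of 0.05 at CAC 0.8, although the pilot found less than 0.02 for large clusters, or the full 0.02 bound at CAC as low as 0.5.

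Two parts do not stand. Moving to 28 county-period records does not help by itself: grouped binomial counts have the same likelihood as individual binary data and still have no free residual. And this is not only absent detail, since the article does state which county-level adjustment it makes, and the standard way to fit that adjustment omits the variance that matters.

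**Conclusion.** The concern holds conditionally. If the named adjustment is fitted as a single county random intercept in a binomial model, the arm-by-period test exceeds its nominal 5% whenever CAC is below 1. For caries the excess is modest at high CAC (7.5% at 0.95) and material at 0.8 or lower. For whole-population process outcomes it is serious even with very stable counties: at ICC 0.02, CAC must be at least about 0.996 to hold the rate at 10%. At an assumed 40% utilisation, CAC 0.95 corresponds to a county-period standard deviation of only √(0.02 × 0.05 × 0.24) = 0.015, or about 1.5 percentage points.

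These figures rest on assumed CAC values, equal county sizes, no weighting, and, for process outcomes, an ICC at the pilot's upper bound. Smaller ICCs or denominators lower them. With CAC equal to 1, or with a county-by-period effect in the model, there is no such inflation.

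**What to change.** In the Statistical analysis plan section, state that the models for binary impact and process outcomes include a county-by-period random effect in addition to the county effect, and that the arm-by-period term is tested on county-level degrees of freedom (about 12). Alternatively, analyse the 14 county changes with a t test or a county-level permutation test.

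This costs a sentence of wording and no new data. Confidence intervals will be wider than under an intercept-only model. For caries, take a fall from 25% to 10% in the test counties, no change in the controls, and variance 0.6525 × [0.05(1−CAC)/7 + 0.95/560], where 0.6525 is the sum of p(1−p) over the four arm-periods. Power for the change contrast on 12 df is then about 86% at CAC 0.8 and 65% at CAC 0.5, against the stated 80%. The CAC assumed should therefore be stated with the power figure.
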